### Randomisation and allocation concealment

An external pilot cluster RCT [56, 57] will be undertaken, seeking to recruit and randomise eight CCRPs (clusters) to a treatment or a control arm in a 5:3 ratio. The randomisation ratio was informed by data emerging from our feasibility study, including the need to ensure that sufficient nurses and patients have EPC exposure to support the aims of the qualitative process evaluation. Randomisation will be conducted using the stratifying variables of CR team setting (hospital-based, community-based, or mixed hospital and community), and monthly throughput of new patients assessed for CR at stages 2–3, facilitating division into small and large teams. Team setting has been selected as a stratifying variable because our feasibility study suggested that teams working in hospital and community settings may encounter different resource issues that could affect the delivery of EPC. Throughput of new patients into CR services has been selected as a stratifying variable, as this is an indicator of team workload, and will ensure that sufficient participants are recruited into each trial arm.

Randomisation will be carried out by a statistician, independent from the researchers recruiting CR teams, using computer-generated random numbers. A cluster randomised design, as opposed to individual participant randomisation, is essential to avoid contamination between trial arms (i.e. intervention participants coming into direct contact with controls and sharing aspects of their treatment). Our EPC intervention involves training CR nurses to apply mental health care coordination with embedded participant-led BA. Once trained, it would be very difficult operationally for the nurse to apply structured care coordination to only a subset of eligible participants (as would be required with individual randomisation).

### Settings and study population

#### CCRP recruitment procedures

Eight locality-based CCRPs in South West England will be recruited and randomised. Teams who took part in the feasibility study will be excluded. A two-stage approach to local CCRP recruitment will be employed. We will write to the lead CR nurse in each of the 20 operationally distinct CCRPs in South West England providing detailed information about the study and inviting their participation. In each of the geographical areas the recruitment letter will be co-signed by the trial chief investigator and the local co-applicant. Each team indicating an interest in participation will receive a briefing visit, where the trial design and methods will be explained by the researcher, and the staff will be given an opportunity to ask questions about what might be involved, before being asked to provide written consent to participate in the study.

Nurses in teams allocated to the CCRP with EPC intervention arm will receive EPC and self-harm risk management training (total of two full days) before they start to recruit patients. EPC-trained nurses will be supervised regularly by experienced specialist clinicians/BA practitioners.

#### Participant eligibility criteria

A pragmatic approach will be adopted, whereby adult patients (aged 18 years or over) referred for CR based on local clinical referral protocols will be screened (stages 2–3) for eligibility. The majority will be individuals previously admitted with an ACS (unstable angina, non-ST-elevation MI or ST-elevation MI) or following a coronary revascularization procedure (percutaneous coronary intervention (PCI), coronary artery bypass grafting (CABG)), with or without heart failure [61]. Patients with a new episode of depressive symptoms identified through nurse screening at the start of CCRP using the PHQ-9 [58, 62] (score 10 or more) are potentially eligible for inclusion. Patient exclusion criteria include: individuals reporting having been actively treated for depression (psychological or drug therapy) within the previous 6 months, or where there is evidence of alcohol or drug dependency, being acutely suicidal, or having poorly controlled bipolar disorder or psychosis/psychotic symptoms based on a clinical review (seeking external confirmation from the GP or other clinicians as required). No language exclusion will be applied; we anticipate that the majority of patients will have sufficiently good English language skills to engage with EPC. However, consistent with routine practice in delivering psychological therapy, NHS translation resources will be employed to assist participants where required.

#### Patient participant recruitment procedure

The CR nurse will apply a structured checklist to ascertain participant eligibility based on our inclusion/exclusion criteria. Eligible participants will be invited to take part in the trial by the CR nurse, and given brief study information to take away and review. The nurse will also ask permission to pass the individual’s contact details on to the study researcher. The researcher will then contact the patient within 7 days to discuss study participation and provide them with a detailed Participant Information Sheet. The researcher will arrange to visit the potential participant to obtain written consent and baseline assessment before the participant commences CCRP (stage 4). Potential participants will be reminded of their right to refuse participation, or to withdraw from the study at any time without it affecting their clinical care.

### Sample size

Using UK national audit data (2010–2011), 55,452 patients (for MI, PCI, CABG) undertook phase 3 CR from 280 teams: an average of 200 patients per team per year. Assuming 17 % have depressive symptoms [27], this equates to 35 eligible patients per team each year. The participant consent rate will be established through piloting as no relevant UK data, applicable to cluster trials, are available. Two RCTs (individual randomisation) from the US, exploring psychological/drug therapy in cardiac rehabilitation settings, observed highly variable consent rates of 85 % (150/177 – Vanguard CODIACS study) [51] and 37 % (2481/6854 – ENRICHD study) [49]. Based on the patient throughput and rates of depressive symptoms observed in our feasibility study, and an assumed participation rate of 50 %, we aim to recruit 64 patients through the eight teams in 6 months. This sample size is sufficient to estimate a follow-up percentage as low as 50 % with margin of error ±12.8 % based on the width of the 95 % confidence interval (CI), and as high as 90 % with a margin of error of ±9.3 % based on the lower bound of the 95 % CI. We do not plan to use estimates from the pilot of the intra-cluster (intra-CR team) correlation coefficients (ICCs) for key outcomes to plan the sample size for the definitive trial as the pilot sample is small and estimates will be imprecise. Using national audit data (2010–2011; 6272 patients; 119 CR teams), we estimate the ICC for depression to be 0.047 (95 % CI: 0.034 to 0.062). This ICC estimate and CI will be used to inform the sample size calculations for the definitive trial.

### Data collection

Participants in both arms will complete baseline measures prior to commencing CCRP, and then two face-to-face follow-up interviews with a researcher at 5 and 8 months post randomisation (Fig. 2). Blinding of patients, practitioners or researchers extracting data on study outcomes is not possible in this cluster design, but the final analysis will be carried out by a statistician who is blind to treatment allocation. Data will be collected on process measures, patient-reported outcomes, and resource use and costs.

#### Process measures

Process data relating to participant throughput and intervention fidelity will be collected.

To ascertain study eligibility and recruitment we will ask CR nurses to report the numbers of patients: attending an initial CCRP nurse assessment, the proportion identified with depressive symptoms during this assessment, the prevalence of ‘new onset’ (as opposed to existing) depression and the number of patients who were eligible for study participation. Of eligible patients, we will describe: the number offered study entry; the number who later agreed to be contacted by a researcher; and who subsequently consented to take part and underwent a baseline interview with a researcher. We will also capture data on participant socio-demographic characteristics (age, sex, ethnicity/preferred language) and clinical condition resulting in a CR referral to document how well we have engaged with service users from diverse backgrounds, such as non-English speakers.

Intervention fidelity will be established through a structured notes review documenting the numbers of participants recruited who do not attend CCRP and the proportion with documentary evidence of care coordination in their notes. For participants engaging with the EPC intervention, we will assess adherence by recording the number of BA sessions offered and the number of sessions attended, the number of participants with documentary evidence of care coordination on exiting CCRP, and the type of psychological referrals made (if appropriate).

#### Participant-reported outcomes measures

Measures are selected on the basis of evidence of their validity in this population, and to ensure coverage of key areas from a clinical and patient perspective (with input from our lay and clinical advisors).

##### Baseline assessment only

This assessment includes some measures that will not be repeated at follow-up. The revised clinical interview schedule (CIS-R) [63, 64] will be administered to ascertain a clinical diagnosis of depression. This score will not determine study eligibility, but will allow its comparison to the other patient-reported measures of depression symptom severity ascertained using the Beck Depression Inventory (BDI-II) (described below). Some short questions to ascertain, and account for, participant treatment preferences [65] will be included. We will extract data from clinical records (GP, CCRP) relating to known cardiac risk factors (body mass index (BMI), blood pressure, glycosylated haemoglobin (HbA1c), lipids, smoking status) as recorded at the participant’s latest clinical assessment prior to recruitment.

##### Baseline and follow-up measures

Although we will request that NHS providers inform us of any participant deaths, we will also tag their NHS records to ensure we capture any cardiac- and non-cardiac-related deaths between baseline and the 8-month follow-up. At the last follow-up we will also request that the date and last recorded known cardiac risk factors in CCRP records are extracted. At the same time we will contact the participant’s GP to request that they extract the same data from primary care records, and that they summarise the incidence of any new cardiac events, i.e. death and/or hospital admissions for ACS or revascularisation procedures (CABG or PCI), or mental health events (e.g. self-harm, suicidality) arising since study enrolment. In addition to being outcomes, these data will be part of the safety monitoring of serious adverse events (SAEs) and adverse events (AEs).

The baseline and follow-up interviews will include self-reported cardiac- and non-cardiac- related morbidity and smoking status, antidepressant medication use [66], and resource use. Depressive symptoms will be measured using the BDI-II [67, 68], a 21-item self-report instrument measuring symptom severity with an emphasis on affective and cognitive symptoms. Higher scores represent greater depression severity (range 0–63), and minimal (0–13), mild (14–19), moderate (20–28) and severe (29–63) symptom severity ranges have been specified. The Beck Anxiety Inventory [69, 70] will be applied as anxiety is commonly comorbid with depression. This 21-item, self-report measure asks patients to report anxiety symptoms over the last week from 0 (none: it did not bother me at all), 1 (mildly: it did not bother me much), 2 (moderately: it was very unpleasant, but I could stand it), and 3 (severely: I could barely stand it). Item scores are summed with total scores of 8–15, 26–25, and 26–63 taken as cut-off points defining categories for mild, moderate, or severe anxiety respectively. Health-related quality of life will be assessed using both generic and disease-specific measures. The 5-item EuroQoL (EQ-5D) [71] is a standardised generic measure of health-related quality of life, which is suitable for use in people with a wide range of health conditions, and is recommended by NICE for economic evaluations alongside clinical trials. We will also administer the HeartQoL [72, 73], a tool comprising 14 items, with 10-item physical and 4-item emotional subscales, which are scored from 0 (poor health-related quality of life) to 3 (better). To assess when and how participants become activated over the course of their EPC, we will administer the 9-item Behavioral Activation for Depression Scale – Short Form (BADS-SF) [74] at baseline, and the 5-month and 8-month follow-up assessments. The BADS-SF is a 9-item tool, where each item is rated from 0 (not at all) to 6 (completely). The total score ranges from 0 to 54, with high scores representing greater activation. Finally, participant experiences of care will be assessed at the 5-month follow-up only, using the 8-item, self-reported Client Satisfaction Questionnaire (CSQ-8) [75] and an adapted version of the NHS Friends and Family Test (FFT). The CSQ items use a 4-point Likert scale (1 to 4) response set, with the total scores ranging from a possible 8 to 32; and higher values indicating greater satisfaction. The FFT consists of a single item with a 5-point rating scale (‘Extremely likely’ to ‘Extremely unlikely’) and two free-text items (‘What was good about your experience?’ and ‘What would have made your experience better?’).

### Economic evaluation

The analytical perspective of NICE’s decision-making is a societal costing perspective. The pilot study will test methods of resource and service use data collection enabling estimation of the costs to the NHS, costs to social care and PSS, and relevant costs to patients and their carers/families (including NHS and privately funded mental health care). Wherever feasible, these will distinguish use of services for (1) depression or anxiety; (2) for other mental health problems; (3) for other health reasons or social needs. A preliminary assessment of the cost of providing EPC within CR will be undertaken. Service use data will be collected from routine/administrative sources (e.g. hospital records, GP records, community mental health team records, social care records) and participant self-report using the Service and Resource Use Questionnaire (SRUQ). The SRUQ will be adapted from the Client Services Receipt Inventory [76], with input from our lay advisors. The completeness, validity and reliability of participant-reported versus routine administrative data will be compared in relation to the types/amounts of health care/service used over the follow-up periods planned for a definitive trial.

#### Statistical analysis plan

Trial data will estimate CR team recruitment and patient study completion rates. As this is a pilot study we will not report definitive estimates of effectiveness and costs; our primary aim is to document the adequacy of trial procedures, intervention acceptability and outcome measures. All pilot study data will be collected [77] and reported according to the CONSORT extension for cluster randomised trials [78]. Recruitment, intervention and control uptake, outcome completion rates, and drop out will be reported (with 95 % CIs). We will compare the recruitment rate and participant characteristics at baseline between the trial arms to assess whether there is evidence of selection bias resulting from (cluster) randomising teams before participant recruitment [79]. Patient outcome data (including resource use) will be analysed descriptively (e.g. means, standard deviations (SDs)) for each arm at each follow-up and we will report outcome effect sizes (i.e. between-group mean differences and 95 % CIs) based on an intention-to-treat analysis. We will explore the impact of patient preferences documented at baseline in the analysis. We will also conduct an exploratory sensitivity analysis reporting between-group outcomes in the sub-groups of patients who do, or do not attend, cardiac rehabilitation programmes.

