Most intervention studies have recruited participants immediately following an acute cardiac event, and the complexity of depression in that period may have contributed to the lack of treatment response. The reasons for the limited benefits of conventional depression treatments in patients with coronary disease are not clear. First, depression that starts after an ACS is different from depression in the general population. Post-ACS depression does not have the usual risk factors as seen in the general population, but is associated with ongoing cardiac symptoms, and increased concerns about health [10, 11], which may act to reduce the response to conventional treatment [45]. Second, conventional psychological treatments, such as CBT, that encourage recall of past experience and that challenge maladaptive thoughts, may be too traumatic for people who have suffered a recent, serious threat to life. Third, conventional psychological therapies available through IAPT are considered expensive and may not be widely available to patients with CHD. Indeed, a recent qualitative study of patients [52] concluded that management of depression should be embedded within CR teams rather than as another source of referral. UK CR programmes experience significant patient attrition at each stage of the rehabilitation pathway, with over half of patients dropping out before locality-based CCRP commences. Given this attrition, for the 17 % of patients with depressive symptoms who actually attend at least one assessment with a CCRP, ‘another outward referral’ for psychological care may simply be a further barrier to accessing timely care. If a low-intensity psychological treatment, such as BA, has the potential to be safely and effectively [38, 40–42, 53, 54] embedded within the CCRP, this could holistically tackle the depressive symptoms at the same time as physical rehabilitation as part of patient case management. Similarly, acknowledging that attrition from rehabilitation is high even in patients who attend an initial CCRP assessment, we also believe that any attempt to enhance psychological care should include training CR nurses (who routinely screen for depressive symptoms) to apply evidence-based referrals for those who elect not to attend rehabilitation. Such mental health care coordination will also be in place for patients completing CCRP (including BA), but whose symptoms do not respond.

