As part of this care coordination protocol, all participants will be offered nurse-supported self-help using a participant BA manual. The self-help BA manual consists of a structured programme aimed at enabling participants to re-engage with sources of positive reinforcement from their environment and to develop future strategies for managing their depressive symptoms. The manual adopts a functional analytical approach, aiming to help the participant develop an understanding of behaviours that might interfere with meaningful, goal-oriented behaviours (e.g. negative avoidant behaviours). The manual also explains how to self-monitor mood, and then to identify patterns of behaviour associated with their depression. Participants are encouraged to develop alternative behaviours which are goal- orientated, targeting routine, pleasurable, and necessary activities, and activity scheduling of these identified behaviours.

Although our pilot intervention involves a participant-led self-help BA manual, the CR nurses will actively support participants. The CR nurses will attend a 2-day training course delivered by experienced mental health practitioners, during which they will receive training on the key techniques of mental health care coordination, managing safety and risks, and BA. This training will allow nurses to actively support participants during care coordination and as they work through the BA manual alongside their CR programme. Nurses will also be provided with a session-by-session guide, detailing the types of care coordination tasks which might be relevant for participants as they move through their 6–8 week structured programme (Additional file 1). This guide is flexible to accommodate participant preferences for care. Nurses who are delivering EPC to study participants will also receive bi-weekly clinical supervision by an experienced mental health practitioner.

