## Project timeline

The project commenced on 1 April 2014 and is scheduled to complete in July 2016. The feasibility study was reported in May 2015. Preparatory work for the pilot trial, including CR team recruitment, commenced January 2015. Cluster randomisation took place in April 2015, and intervention training delivered to the five CR teams in June–July 2015. Participant recruitment commenced July 2015 and is scheduled to complete by the end of 2015. Follow-up data and qualitative interviews will take place between September 2015 and June 2016. Data analysis will commence in January 2016, with the final report due in July 2016.

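### Comparing arms within rehabilitation attenders and non-attenders conditions on a post-allocation event that EPC could change, so it is open to selection bias and is not a sensitivity analysis of the intention-to-treat result

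*Protocol article*

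**What the plan says.** The Statistical analysis plan section reports between-group mean differences with 95% confidence intervals "based on an intention-to-treat analysis". It then adds an "exploratory sensitivity analysis reporting between-group outcomes in the sub-groups of patients who do, or do not attend, cardiac rehabilitation programmes". No estimand, adjustment or caution accompanies the attendance subgroups. The same section sets the status of all the outcome results: "As this is a pilot study we will not report definitive estimates of effectiveness and costs".

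The order of events is given elsewhere in the article:

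- Project timeline: "Cluster randomisation took place in April 2015" and "Participant recruitment commenced July 2015".
- Patient participant recruitment procedure: consent and baseline come before the structured programme at stage 4.
- Enhanced psychological care (treatment) intervention: the trained nurse sets out the treatment options, including nurse-supported behavioural activation (BA), once an eligible patient is identified at the stage 2–3 assessment. The nurse then supports patients "as they work through the BA manual alongside their CR programme".
- Rationale for current research: "acknowledging that attrition from rehabilitation is high even in patients who attend an initial CCRP assessment", the authors want nurses trained to make referrals for people who choose not to attend.

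**The concern.** Attendance is not a baseline characteristic. It follows allocation, and in the EPC arm it also follows the first contact with a nurse trained to coordinate mental health care and offer BA. The Background describes BA as acting on avoidance and withdrawal, so an influence on attendance is plausible on the protocol's own theory. If EPC brings in some patients who would otherwise have stayed away, EPC attenders include people whose counterparts in the control arm are counted as non-attenders. Neither subgroup contrast then compares like with like.

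The label is a second problem. A sensitivity analysis asks the same question under other assumptions. A contrast confined to attenders concerns a different population from the intention-to-treat comparison, so agreement or disagreement between the two says nothing about the robustness of the intention-to-treat result.

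What is at stake is how one exploratory table is read: a difference in it could be taken for an EPC effect among attenders or non-attenders when it reflects who is in the group.

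**Working it through.** The plan attaches no figure to this analysis, so there is none to reproduce. The margins in the Sample size section concern follow-up percentages and play no part here.

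**Step 1: order of events.** Teams were randomised (April 2015), patients were recruited from July 2015, the EPC nurse acts from the stage 2–3 assessment, baseline is taken, and attendance at stage 4 comes last. Attendance therefore follows both allocation and the start of EPC.

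**Step 2: size of the subgroups.** Inputs: eight patients per team (Abstract), eight teams in a 5:3 ratio (Randomisation and allocation concealment), and 41% of those invited attending (Usual care (control) intervention).

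- Arms: 5 × 8 = 40 and 3 × 8 = 24.
- Attenders: 0.41 × 40 = 16.4 and 0.41 × 24 = 9.84, about 16 versus 10.
- Non-attenders: 23.6 and 14.16, about 24 versus 14.

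The article also says that around half of patients who screen positive do not proceed. That would give 20 versus 12 in each subgroup. Neither percentage describes consenting trial participants.

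**Step 3: precision.** The 95% half-width in SD units, before clustering or loss to follow-up, is 1.96 × √(1/n₁ + 1/n₂).

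- Attenders at 41%: 1.96 × √(1/16.4 + 1/9.84) = 0.79. With rounded counts and t on 24 degrees of freedom: 2.064 × √(1/16 + 1/10) = 0.83.
- Non-attenders at 41%: 1.96 × √(1/23.6 + 1/14.16) = 0.66.
- Either subgroup at 50%: 1.96 × √(1/20 + 1/12) = 0.72.
- Whole arms: 1.96 × √(1/40 + 1/24) = 0.51.

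**Step 4: size of the selection bias, by assumption.** Let a standard normal propensity to attend have correlation r in magnitude with the outcome, with patients less likely to attend scoring worse. Let the true EPC effect be zero. With attendance p_C in control and p_E under EPC, and φ(z_p) the normal density at the cut-off leaving a proportion p above it, the spurious differences are:

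- attenders: r × [φ(z_pC)/p_C − φ(z_pE)/p_E]
- non-attenders: r × [φ(z_pE)/(1 − p_E) − φ(z_pC)/(1 − p_C)]

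Worked case with p_C = 0.41, p_E = 0.61, r = 0.4: attenders 0.4 × (0.948 − 0.629) = 0.13 SD; non-attenders 0.4 × (0.984 − 0.659) = 0.13 SD.

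Across p_C of 41% or 50% and r of 0.2 to 0.4 (r and the rise in attendance are assumed):

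| Rise in attendance under EPC | Attenders (SD) | Non-attenders (SD) |
|---|---|---|
| 0 points | 0 | 0 |
| 10 points | 0.03–0.07 | 0.03–0.07 |
| 20 points | 0.06–0.13 | 0.07–0.14 |
| 30 points | 0.09–0.19 | 0.10–0.24 |

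In this model both subgroups shift the same way, making EPC look worse in each, while the whole-arm difference stays at zero. The direction would reverse if patients less likely to attend scored better.

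A simpler mixture gives a similar size. If attendance rises from 41% to 55% and the extra attenders score 0.5 SD worse (both assumed), the attender contrast moves by (0.14/0.55) × 0.5 = 0.13 SD.

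**The case against.** The strongest reply is that little rests on this table. It is called exploratory, it follows an intention-to-treat comparison, and it sits in a pilot that disclaims definitive effectiveness estimates. Its wording is also milder than for the main outcomes: effect sizes with intervals are promised for the intention-to-treat analysis, whereas the subgroups are only to have between-group outcomes reported, which might mean descriptive figures by arm. Because EPC offers different things to attenders and non-attenders, describing both is a fair feasibility question. Part of the remedy is already planned, since uptake in both arms is to be reported with 95% intervals and the notes review counts recruited patients who do not attend. All of this stands, and it lowers the severity. It does not make the contrast valid, and the text gives no warning against reading it as an effect.

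Two stronger readings are tempting, and the documents support neither:

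- A reader might infer that the comparison *is* biased. That needs EPC to change who attends. The passages make this plausible but do not show it, and no attendance by arm is given.
- A reader might infer that the table would push the definitive trial towards recruiting attenders only. Nothing says it will inform eligibility, and the rationale deliberately includes people who elect not to attend.

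**Conclusion.** The point holds in a limited form. A between-arm contrast within attenders or non-attenders conditions on a post-allocation event that EPC could influence. It is open to selection bias, and it does not test the robustness of the intention-to-treat estimate. The bias is zero if EPC leaves attendance unchanged. Under the assumed rises of 10 to 30 points and r of 0.2 to 0.4 it is about 0.03 to 0.24 SD.

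That is well below the sampling error of roughly 0.66 to 0.83 SD, so in this pilot imprecision would hide the illustrated bias. Small numbers are thus a further reason not to present the contrast as an effect. The subgroup sizes rest on full recruitment, eight patients per team and one of the two general attendance figures. The severity is minor.

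**What to change.** In the Statistical analysis plan section:

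1. Drop the sensitivity-analysis label, and do not report or interpret a between-arm effect within attendance subgroups.
2. Report attendance at the structured programme by arm as an outcome in its own right, with a 95% confidence interval that allows for clustering by team.
3. Describe the outcomes of attenders and non-attenders within each arm, with a caution that these groups are formed after randomisation and are very small.
4. For any between-arm subgroup, use only variables fixed before EPC could act, such as the screening PHQ-9 score or the cardiac diagnosis leading to referral.
5. Do not substitute a complier-type estimate that assumes EPC has no effect without attendance. EPC also reaches non-attenders through care coordination and referral, and patients who would attend anyway are offered BA, so that assumption conflicts with the design.

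The change is to wording only and uses data the plan already collects. The cost is the loss of one exploratory between-arm table.
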